## Abstract

**Background:**

Disparities persist in testing and treatment for hepatitis C virus (HCV), leaving socially marginalized populations, including people who inject drugs (PWID), less likely to benefit from curative treatment. Linkage services are often insufficient to overcome barriers to navigating the medical system and contextual factors.

**Methods:**

The You’re Empowered for Treatment Initiation (YETI) Partner trial is a single-site randomized controlled trial evaluating the efficacy of a two-session behavioral intervention that engages injecting partners as peer navigators for HCV treatment. We aim to recruit 250 PWID and their primary injecting partners in San Francisco, California, randomizing them 1:1 to either a control or intervention group. The primary outcome is the initiation of HCV treatment, with secondary outcomes including treatment completion and sustained virologic response 12 weeks post-treatment. Data will be collected through questionnaires and electronic health records and analyzed using intention-to-treat and mixed-effects models.

**Discussion:**

This trial will provide evidence of a new HCV treatment linkage intervention leveraging the support of primary injecting partners to initiate HCV treatment. If successful, the intervention could inform public health strategies and policies to address HCV in marginalized populations.

**Trial registration:**

ClinicalTrials.gov NCT06179498. Registered on December 22, 2023.

**Supplementary Information:**

The online version contains supplementary material available at 10.1186/s13063-024-08662-0.

## Administrative information

Note: the numbers in curly brackets in this protocol refer to SPIRIT checklist item numbers. The order of the items has been modified to group similar items (see http://www.equator-network.org/reporting-guidelines/spirit-2013-statement-defining-standard-protocol-items-for-clinical-trials/).

## Introduction

### Background and rationale {6a}

In the USA, approximately 45–60% of PWID are estimated to have HCV infection, compared to approximately 1% of the general population [1, 2]. Adults under 30 years of age experience the highest rates of incident HCV infection [3–5]. The recent opioid epidemic has contributed to an increase in young adults injecting drugs [6–8]. In San Francisco, PWID in the last 12 months accounted for only 2.8% of the total population, yet 73.1% of people with anti-HCV antibodies and 90.4% of untreated, active HCV infections in 2019 were among PWID [9]. Given this disproportionate impact, local, national, and global organizations have recognized PWID as a priority population for HCV treatment [10].

Extreme marginalization results in severe hardships for PWID, including poverty, homelessness, and discrimination, leading to distrust of and disconnection from medical systems [11–13]. PWID also typically lack traditional social support networks. Most younger adult PWID inject daily within a social network, establishing close relationships with members of their injecting network. Often, one person assumes the role of the “primary injecting partner,” providing emotional and social support that promotes well-being [14]. Studies demonstrate that having a friend or partner concerned about one’s HCV is significantly associated with treatment initiation [15], and positive concordant couples (i.e., dyads where both partners are living with untreated HCV) often consider sequentially treatment to ensure mutual support [16].

Once HCV treatment has commenced, adherence rates among PWID and former PWID are high [17–21], highlighting the importance of treatment initiation. In 2015, our research group published one of the first papers differentiating primary injecting partnerships from other social connections within injecting networks [14]. We found that primary injecting partners—typically the main person with whom drugs were injected—invested more emotional and monetary resources into the primary injecting relationship compared to other relationships. Partnerships provide physical assistance and positive emotional and social support, improving well-being in the context of marginalization [22–26].

Dyad interventions have been effective in improving health and well-being across various health areas [27–30]. Findings suggest that primary injecting partnerships are an innate resource to be leveraged in interventions aiming to improve health behaviors among PWID [12, 22, 31–33]. Thus, the existing connection between injecting partners offers a promising avenue for supporting PWID in initiating HCV treatment.

Our study, the You’re Empowered for Treatment Initiation (YETI) Partner Study, evaluates a dyad intervention that augments the social support role of one’s primary injecting partner to improve the probability of and reduce the time to initiating treatment among PWID in San Francisco, California.

### Objectives {7}

The primary objective of the study is to estimate the proportion of people newly diagnosed with chronic HCV infection who start direct-acting antiviral (DAA) treatment and the time from enrolment to starting DAA treatment by a randomized group.

H1a: Those randomized to the intervention will have a higher 6-month probability of treatment initiation compared to those in the control group.

H1b: Those randomized to the intervention will have a significantly shorter time to HCV treatment initiation compared to those in the control group.

Secondary objectives are:To measure changes in injecting-related interpersonal factors and partner support factors at 1-week, 1-month, 4-month, and 7-month post-randomization by randomized group.To determine between-group differences in HCV DAA treatment completion and sustained virologic response at 12 weeks post-treatment completion.

#### Trial design {8}

The *Y*ou’re *E*mpowered for *T*reatment *I*nitiation (YETI) Partner study is a non-blinded, parallel-group, two-arm, superiority randomized controlled trial with 1:1 allocation ratio to assess the efficacy of a two-session dyadic intervention to involve injecting partners as peer navigators to HCV treatment.

We aim to recruit and randomly allocate 250 persons living with HCV (“Index participants”) and their primary injecting partners (“Partner participants”) to either a control or intervention group. The primary endpoint is starting HCV treatment; secondary endpoints are treatment completion and sustained virologic response at 12 weeks post-treatment completion (sustained virologic response 12 weeks post-treatment, SVR-12). A description of the overall study design is in Fig. 1 and the schedule of enrollment, interventions, and assessments is in Fig. 2. Eligible PWID with evidence of HCV infection who enroll will be randomized (1:1) to either a control or intervention group. Both Index and Partner participants will participate in all five study visits: baseline (visit 1), 1-week (visit 2), 1-month (visit 3), 4-month (visit 4), and 7-month (visit 5). Questionnaires will be administered to the Index and Partner at all five visits. Intervention session 1 will be administered with the Index participant only at visit 1, and intervention session 2 with both the Index and Partner participants at visit 2. To expand our ability to capture primary endpoint data, participant data will be linked to their electronic health record (EHR) for HCV treatment start date, completion date, and SVR-12. The study protocol (version 1.4, 03/21/2024) follows the Standard Protocol Items: Recommendations for Interventional Trials (SPIRIT) Statement. The trial has been registered at ClinicalTrials.gov (ID: NCT06179498).

**Fig. 1 Fig1:**
[figure not shown]
YETI Partner Study design

**Fig. 2 Fig2:**
[figure not shown]
YETI Partner Study schedule of enrollment, inventions, and assessments

## Methods: participants, interventions, and outcomes

### Study setting {9}

The trial will be conducted in San Francisco, CA, USA. Community-based organizations (CBO) and clinics providing services for PWID will perform HCV diagnostic testing and refer eligible clients. Recruitment sites serve a set of patients diverse in racial and ethnic identities and are in neighborhoods across San Francisco Study activities will take place at a single study site located in the city center close to several CBO sites, multiple transit lines, and social service organizations that serve the focal population. The study site provides private spaces to conduct research activities, secure locations for participants to store their belongings, and food and harm reduction supplies.

### Eligibility criteria {10}

#### Eligibility

PWID with recently diagnosed HCV and their primary injecting partner will be eligible for the study.

Index participant eligibility criteria:18 years or older of age;Self-report injecting drugs within the past month;Have evidence of chronic HCV infection (antibody and RNA reactive) and have been diagnosed after 2016;Have no evidence of HCV treatment initiation, specifically DAA treatment;Self-report having a primary injecting partner whom they are willing to invite to participate in the study;Cognitive capability to provide written informed consent; andEnglish language proficient.

Partner participant eligibility criteria:Identified and invited to participate by the Index participant;18 years or older of age;Cognitive capability to provide written informed consent; andEnglish language proficient.

Index participant exclusion criteria:Previous participation in this research study (i.e., Partner participants are unable to enroll as Index participants)Under 18 years of age at enrollmentIntention to move outside of San Francisco in the next 6 months

Partner participant exclusion criteria:Previous participation in this research study (i.e., Index participants are unable to enroll as Partner participants)Under 18 years of age at enrollment

#### Eligibility screening process

When a referred client contacts the YETI Partner study, staff will confirm study eligibility, collect contact information, and schedule a study visit. Referred clients will be able to contact the YETI Partner study via telephone, email, and in person at the study site.

### Who will take informed consent? {26a}

#### Written consent to participate

Eligible participants (Index and Partner) who present in-person at the study site for visit 1 will individually undergo a fully informed written e-consent protocol led by trained study staff. Research participants should be able to understand, as completely as possible, what procedures, risks, benefits, alternatives, and rights are involved, and make an informed choice about being in the study without pressure or undue inducement to participate.

During this process, consent will be requested for (a) study participation and (b) the release of medical records for up to 5 years post-participation. To help protect our participants’ privacy, we have received a Certificate of Confidentiality from the National Institute of Health. Our consent form and plain language companion document, approved by the IRB at our university, were developed in partnership with members of our community-academic partnership through a series of group discussions focused on improving readability and transparency. Directly after voluntary consent is obtained and documented on REDCap, participants will begin visit 1. REDCap (Research Electronic Data Capture) is a secure, web-based software platform designed to support data capture for research studies, providing (1) an intuitive interface for validated data capture; (2) audit trails for tracking data manipulation and export procedures; (3) automated export procedures for seamless data downloads to common statistical packages; and (4) procedures for data integration and interoperability with external sources [35, 36]. Study data were collected and managed using REDCap electronic data capture tools. Those who decline study enrollment will receive information about HCV prevention strategies and HCV treatment resources and will be paid $5 for their time.

### Additional consent provisions for collection and use of participant data and biological specimens {26b}

This trial does not involve the collection or storage of biological specimens. As such, there are no provisions or protocols for their handling within this study.

## Interventions

### Explanation for the choice of comparators {6b}

The comparator—control arm—is information about HCV prevention strategies and HCV treatment resources. In partnership with CBOs and clinics providing HCV testing and results disclosure, we will use existing materials from organizations that provide HCV testing. These materials will provide details about prevention and care which includes (a) preventing further harm to their liver, (b) reducing risks for transmitting HCV to others, and (c) undergoing medical evaluation for liver disease and possible treatment. Standard of care information focuses on information and transmission risk reduction for the individual.

### Intervention description {11a}

In addition to the standard of care HCV prevention and care handout that the control arm receives, the intervention arm participants will receive two counseling sessions (see Table 1). The intervention is manualized, with session 1 involving the Index participant only, and session 2 involving both Index and Partner participants. Each session will be led by a study staff member who is a certified HIV/HCV test counselor in California and has received additional training in motivational interviewing. Staff are trained in using the HCV Treatment Navigation Map (Navigation Map). The Navigation Map is a printed, fillable “map” comprising self-identified priorities, the steps that the Index participant will identify toward HCV treatment initiation, and the support that the Index participant will identify needing from their primary injecting partner towards treatment initiation.

**Table 1 Tab1:** Intervention session information

Intervention session	Timepoint	Participant(s)	Focus
1	Visit 1	Index only	(a) Set HCV treatment as a priority goal (b) Outline Navigation Map
2	Visit 2	Index and partner	(a) Engage Partner in Index’s HCV treatment initiation plan (b) Complete the Navigation Map with Partner

#### Session 1

Index participants will receive a ~ 30-min, in-person, one-on-one counseling session led by study staff to begin filling in their individual Navigation Map (see “Protocol”). During this process, the staff member will strategically engage the participant in a series of open-ended questions that correspond to consecutive sections of the Navigation Map to build dyadic capacity for supporting the Index to start HCV treatment. Dyadic capacity depends on interpersonal factors (e.g., intimacy) and partner involvement (e.g., tangible support). Session 1 focuses on the Index participant, their situational challenges, and their individual and relational strategies or supports for treatment initiation. Study staff will use discussion probes to cultivate dialogue about past situations where the Index participant and their partner provided support (partner involvement) for other priority activities (e.g., accessing harm reduction materials or securing housing), and the strategies they employed to overcome perceived obstacles in similar situations. The study staff will engage the recently diagnosed Index participant to (a) assess HCV treatment as a priority goal, (b) outline the “HCV Treatment Navigation Map” with potential situational and contextual challenges and strategies and align priorities with motivation for HCV treatment, and (c) brainstorm how their Partner participant can support their treatment initiation.

#### Session 2

Session 2 builds on the progress made in increasing overall partner support and emphasizing the Partner’s role in tailoring support for the Index to begin HCV treatment. Study staff will facilitate a 40–60-min, in-person discussion-based activity with the Index and Partner participants that builds upon the Session 1 information. First, the research staff will assist the Index in sharing the Navigation Map from session 1 to review perceived barriers and facilitators to HCV treatment initiation. Session 2 will focus on (a) collaboratively reviewing the Navigation Map with the Index and Partner, (b) outlining and discussing preliminary strategies and timeline towards treatment initiation, and (c) role-playing and practicing strategies to concretize a plan involving both partners. Study staff will then facilitate a discussion between the Index and Partner to collaboratively devise ideas and strategies to overcome each barrier, drawing upon support strategies identified earlier (partner involvement). The Partner will also have an opportunity to fill out their own Navigation Map, highlighting ways that they can support the Index. By the end of session 2, the Index participant’s Navigation Map will list possible partner involvement strategies layered on top of challenges identified by the Index participant during Session 1. If time permits, the Index and Partner will practice applying one or two strategies to a hypothetical situation to gain confidence and familiarity.

In situations where the Partner is unable to attend session 2, facilitation will be adapted to focus on Index-only perspectives about past partner involvement and support to overcome challenges. The study staff will use the “Empty-Chair technique” whereby the staff facilitates session 2 activities based on the Index participant’s perceptions of how the Partner participant will respond in preparing the Index participant to engage the Partner for support in navigating HCV treatment. The Index participant will leave with a completed Partner Navigation Map and prompts to introduce the strategies to their partner.

### Criteria for discontinuing or modifying allocated interventions {11b}

There will be no special criteria for discontinuing or modifying allocated interventions, other than participants voluntarily withdrawing from the study or being lost to follow-up.

### Strategies to improve adherence to interventions {11c}

The intervention will be delivered in two in-person counseling sessions held 1 week apart. Adherence in this context refers to attending and completing the two planned study sessions. To support this objective, we will incorporate several strategies rooted in our experience working with PWID and conducting dyadic studies to maximize participant retention.Outreach: Using regularly updated contact information, study outreach workers will maintain participant contact via e-mail, social media, text messaging, phone calls, and visiting frequented physical locations.Incentives: Cash payments will follow an incentive structure suggested by our community-academic partnership.Relationships with Community Collaborators: To expand study outreach and assist with locating, we will provide CBO partners monthly with a list of participants with outstanding visits.

### Relevant concomitant care permitted or prohibited during the trial {11d}

Implementation of the intervention will not require alterations to the usual care pathways—standard of care HCV prevention and care handouts—and these will continue for both trial arms. The study will not interfere with or restrict participants’ access to usual care, ensuring that all standard services remain available throughout the trial.

### Provisions for post-trial care {30}

There is no anticipated harm for trial participation, and participants will be compensated for their time and involvement in the study.”

### Outcomes {12}

The primary outcome of this trial will be the initiation of HCV treatment within the study period. Secondary outcomes will include (a) completion of HCV treatment; and (b) achievement of SVR12. All outcomes will be measured within 2 years of enrollment. Individuals without evidence of an HCV-associated visit or without indication of DAA treatment prescribed will be considered to have not started HCV treatment. Outcomes will be assessed using data from questionnaire responses and EHR integration.

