### Sample size {14}

The primary superiority hypothesis for this trial, that those randomized to the intervention will have a higher 6-month probability of treatment initiation compared to those in the control group, was powered based on our previous work and comparable results of community-based RCT studies with PWID that suggest a HCV treatment initiation rate of 30% for those in the intervention group (13% in control group), and a retention rate of 80% (based on our previous cohort of injecting partnerships) [37, 38]. We will have 80% power to detect this effect with a sample size of 250, corresponding to a risk ratio of 2.0, at the 5% significance level.

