Given the randomized design, the primary comparison will include the cumulative incidence and risk ratios with 95% CI for HCV treatment initiation by Index participants at 6 months post-enrollment and across the entire follow-up period by randomization group. We will use a survival framework that acknowledges loss to follow-up with at-risk time beginning at study enrollment and censoring at the date of the final attended follow-up visit. The event of interest is HCV treatment initiation using a known or self-reported date of HCV treatment initiation.

Secondary analyses will include comparisons of other treatment completion and SVR12 by randomization group, with subgroup analyses for a stratum of Index ≤ 30 years of age, gender, race, and ethnicity.

While all Index participants will be living with untreated HCV at the time of study enrollment, some injecting partners will also have untreated HCV infection and may benefit from intervention involvement. Exploratory analyses will measure differences in the probability of initiating HCV treatment for HCV-infected partners by randomized group.

An exploratory linear mixed model (LMM) will assess the putative mechanisms of action by which changes in partner support and interpersonal factors (over time and by group) impact HCV treatment initiation.

Additional secondary exploratory analyses with intact dyads where both partners have data on the same independent variables will enable the investigation of partnership-based research questions that explore how relationship dynamics affect behavior change in partnerships. Therefore, we will extend the mixed models described above to include actor and partner effects for the continuous partner support variables. This technique illuminates the effects that partners in injecting partnerships can have on both their own and their partner’s behavior. Estimation of separate actor and partner effects will enable us to use contrasts to test whether partner effects are greater in magnitude than actor effects. α will be set at 0.05 for these exploratory analyses.

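### The primary outcome has no single time window: 6 months in the hypothesis and sample size, the study period (up to 2 years) in the outcome definition, and both in the primary comparison

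*Protocol article*

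**What the plan says.** All references are to the Protocol article.

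- **Outcomes {12}** defines the endpoint without a month: "The primary outcome of this trial will be the initiation of HCV treatment within the study period". It then adds "All outcomes will be measured within 2 years of enrollment". Six months is not mentioned there.
- **Objectives {7}** begins "The primary objective of the study is to estimate the proportion of people newly diagnosed with chronic HCV infection who start direct-acting antiviral (DAA) treatment". Time to starting treatment belongs to the same primary objective. Two hypotheses follow. H1a is "Those randomized to the intervention will have a higher 6-month probability of treatment initiation compared to those in the control group". H1b is "Those randomized to the intervention will have a significantly shorter time to HCV treatment initiation compared to those in the control group".
- **Sample size {14}** gives one hypothesis the primary label: "The primary superiority hypothesis for this trial, that those randomized to the intervention will have a higher 6-month probability of treatment initiation". The 250 participants, 80% power and 5% level belong to it.
- **Statistical methods {20a}** describes the primary comparison as cumulative incidence and risk ratios "at 6 months post-enrollment and across the entire follow-up period by randomization group". Time at risk starts at enrollment and is censored at the last follow-up visit attended.
- **Participant timeline {13}** schedules the last visit at 7 months. **Data sources** under {18a} says health-record data are requested every 3 months.

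**The concern.** The section that defines the primary outcome and the section that powers it name different endpoints, and the analysis section adopts both windows. A later analysis plan could choose one, but it would then contradict at least one of these sections. The protocol text itself therefore needs correcting.

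The choice matters because of the intervention's shape: two sessions a week apart, at the start of follow-up. It might raise the number who ever start treatment, or it might mainly bring forward starts that controls make later. A 6-month comparison credits both. A 2-year comparison credits mainly the first. If the two results disagree, the text lets either be presented as the primary one.

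A further ambiguity is what the whole follow-up means. Censoring at the last attended visit points to about 7 months. The 2-year sentence and the health-record linkage point to 24 months.

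**Working it through.** **1. What the sample size is built on.** Inputs from Sample size {14}: 13% control, 30% intervention, 5% level (two-sided assumed, as sidedness is not given), 80% power, 80% retention.

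Uncorrected n per arm = [1.96·√(2·0.215·0.785) + 0.8416·√(0.30·0.70 + 0.13·0.87)]² / 0.17² = 90.5, so 91.

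Continuity-corrected n = (90.5/4)·[1 + √(1 + 4/(90.5·0.17))]² = 101.9, so 102 per arm, 204 in total. Then 204/0.80 = 255, against 250 stated. With 100 retained per arm the corrected power is 79.1%. The plan's figure is reproduced, and it belongs to the 6-month endpoint. (The section quotes a risk ratio of 2.0, while its own rates give 0.30/0.13 = 2.31. That is a separate matter; 2.31 is used here.)

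**2. How far the windows can differ.** The documents give no rates beyond 6 months. I assume a constant control hazard, so control risk at t months is 1 − 0.87^(t/6). For the intervention arm I take two cases: the effect stops at month 6, or hazards stay proportional (hazard ratio ln 0.70 / ln 0.87 = 2.56).

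| Window | Control | Intervention, effect stops at month 6 | RR | Intervention, proportional hazards | RR |
|---|---|---|---|---|---|
| 6 months | 13.0% | 30.0% | 2.31 | 30.0% | 2.31 |
| 7 months | 1 − 0.87^(7/6) = 15.0% | 1 − 0.70·0.87^(1/6) = 31.6% | 2.11 | 1 − 0.70^(7/6) = 34.0% | 2.27 |
| 24 months | 1 − 0.87^4 = 42.7% | 1 − 0.70·0.87^3 = 53.9% | 1.26 | 1 − 0.70^4 = 76.0% | 1.78 |

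Power of a two-sided 5% test of two proportions without continuity correction, at 100 and 125 per arm:
- 6 months: 84% and 91%.
- 7 months, effect stops at month 6: 80% and 88%.
- 24 months, effect stops at month 6: 35% and 42.5%.
- 24 months, proportional hazards: above 99% at both sizes.

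**3. Error rate, on a condition the document does not state.** Suppose success could be claimed on any of the 6-month risk, whole-period risk and log-rank tests, each at an unadjusted two-sided 5%. Simulation under the null used 20,000 runs per setting, 100 or 125 per arm, exponential times, a 6-month rate of 13% or 21.5%, and no dropout. The chance of at least one false positive was:
- follow-up to 7 months: 6.6% to 7.1%;
- to 12 months: 8.5% to 9.0%;
- to 24 months: 9.5% to 10.3%.

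Repeat runs at 125 per arm came out slightly lower (6.4% to 6.7% at 7 months, 9.3% at 24 months), so I round to 6.5–7% and 9–10%. For three independent tests the figure would be 1 − 0.95³ = 14.3%. The overlap between these tests keeps it lower. The 6-month test alone stays at about 5%.

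**The case against.** The strongest reply is that Sample size {14} already settles the matter. It names one primary superiority hypothesis, the 6-month probability, and ties the 5% level to it. The 2-year sentence covers every outcome, including sustained virologic response, and can be read as an outer limit on data collection. With censoring at the last attended visit, the whole follow-up is about 7 months, and there the two windows barely differ (2.11 to 2.27 against 2.31).

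Much of this stands. It shows which endpoint the other sections should be aligned to, and that the discrepancy is small on the 7-month reading. It does not remove the contradiction. Outcomes {12} still defines the primary outcome without 6 months, and Statistical methods {20a} still places both windows inside the primary comparison.

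A reader might infer more: that the trial has several co-primary comparisons, each free to claim success at 5%. The document does not support that. It does not use the term co-primary, and it states no rule that any one result suffices. It asks for risk ratios with confidence intervals, and outside the sample size it sets a 0.05 level only for exploratory analyses. An order of testing may also sit in the detailed analysis plan announced in {20a}. H1b's rank is unclear, but that does not make it a route to success.

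**Conclusion.** The contradiction in the primary outcome window holds on the text alone and needs correcting. Three windows are in play: 6 months, about 7 months by attended visits, and 2 years. H1b also sits under the primary objective with no stated rank.

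How much it matters depends on what the whole follow-up means. On the 7-month reading the effect on the risk ratio is small. On the 2-year reading the risk ratio could be anywhere from 1.26 to 1.78. Those values rest on a constant hazard from the plan's 6-month rates, and the lower one also needs an effect that ends exactly at month 6. Neither assumption comes from the documents, so the low power at 24 months should not be quoted without the proportional-hazards case, where power exceeds 99%.

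The error-rate figures (about 6.5–7% at 7 months, 9–10% at 24 months) apply only if any single unadjusted test could carry the claim. They are a reason to rank the comparisons, not a demonstrated fault.

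**What to change.** - **Outcomes {12}:** define the single primary outcome as DAA initiation within 6 months of enrollment, the endpoint already powered. Enrollment is the time origin that {20a} already uses. Keep the 2-year window for treatment completion and SVR12.
- **Statistical methods {20a}:** limit the primary comparison to the 6-month risk ratio. Label the whole-period risk ratio and time to initiation (H1b) as secondary, and word Objectives {7} to match.
- **Same section:** state whether the whole follow-up runs to the last attended visit (about 7 months) or to 2 years through health records, and set the censoring rule to match.

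A fixed testing order for the two secondary comparisons is optional.

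**Cost:** wording in these sections and an update of the registry entry if it differs. The stated sample size and power are unchanged. H1b and the whole-period comparison lose primary status.

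Keeping several primary tests would cost more. With a Bonferroni split and the continuity-corrected formula, two tests need 244/0.80 = 305 enrolled and three need 266/0.80, about 333. At 250 enrolled, power on the 6-month test would be about 70% or 64%.
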